## Abstract

**Objectives:**

Painful diabetic peripheral neuropathy (DPN) is often refractory to conventional medications. Triple-nerve decompression was proposed for painful DPN due to the frequent involvement of multiple nerve entrapments in diabetes. However, the role of decompressive surgery remains controversial. This trial aims to assess the efficacy of triple-nerve decompression for patients with painful DPN suggestive of nerve entrapment using a randomized controlled trial (RCT) design.

**Methods and analysis:**

This trial is a single-center RCT and will be conducted in Shanghai Ninth People's Hospital. Enrolled subjects (*n* = 74) with painful DPN due to nerve compression, which can be detected by nerve conduction studies, will be randomly allocated at a 1:1 ratio into surgical and non-surgical groups. The primary outcome will be measured by 50% responder rates, which is defined as the proportion of subjects with at least 50% reduction of the mean weekly visual analog score (VAS) of pain from baseline after 6 months of treatment. Mean weekly VAS will be additionally evaluated 1 week (W1), 1 month (M1), and 3 months (M3) after treatment to monitor the changes in pain intensity. The secondary outcomes include two-point discrimination (TPD), Toronto clinical scoring system (TCSS), electrophysiological indexes, hospital anxiety and depression scale (HADS), and the medical outcome study short-form 36-item questionnaire (SF-36). A quantitative analgesic questionnaire (QAQ) will be used as a secondary outcome to quantify the analgesic medication weekly. TPD and TCSS will be conducted at W1, M1, M3, and M6 after treatment. Electrophysiological tests, HADS, and SF-36 will be performed at M3 and M6.

**Ethics and dissemination:**

Ethics approval has been obtained from the Ethics Committee of Shanghai Ninth People's Hospital (SH9H-2-21-T323-2). It was registered on the Chinese Clinical Trial Registry website (http://www.chictr.org.cn) on 16 August 2021 with the number ChiCTR2100050049. Written informed consent will be obtained from all participants. The results of this trial will be disseminated *via* peer-reviewed journals, mass media, and presentations at national and international academic conferences.

## Introduction

Diabetic peripheral neuropathy (DPN) is one of the most common complications of diabetes, affecting up to 50% of patients with diabetes (1). The clinical manifestations of DPN vary greatly and the involvement of the lower extremities is more common than that of the upper extremities. As the most distressing symptom of DPN, neuropathic pain adversely affects the quality of life and is the main reason prompting patients to seek medical treatment (2).

The DPN has long been viewed as a progressive and irreversible disorder. In addition to intensive glycemic control and lifestyle modification, the management of painful DPN remains largely symptomatic. However, the efficacy of conventional medication therapy is limited, and the side effects are usually unbearable (3). Faced with this dilemma, surgical interventions, such as nerve decompression and spinal cord stimulation, had been developed as alternative treatment options for painful DPN. Triple-nerve (posterior tibial nerves, common and deep peroneal nerves in bilateral lower extremities) decompression was proposed based on the following observations from either animal or clinical studies: (1) Peripheral nerves in diabetes are susceptible to chronic compression (4, 5); (2) sites of nerve compression in lower extremities have been identified in anatomic studies (6–8); and (3) axons are more prone to be compressed distally when a proximal compression is present along the same axon, and vice versa (“double-crush” theory) (9). Furthermore, at the molecular level, the neuronal response to hyperglycemia through the sorbitol-aldose reductase or polyol pathway should be appreciated to understand the mechanism of nerve compression in the diabetic population. The sorbitol pathway begins with aldose reductase; an enzyme needed to process cellular glucose for energy production. It makes only a small proportion of sorbitol from residually available glucose under physiological conditions. In chronic hyperglycemia, the hexokinase enzyme, which converts the bulk of intracellular glucose to glucose-6-phosphate, becomes fully saturated, and excess glucose is converted to sorbitol by aldose reductase. Due to its characteristic of low plasma membrane permeability, sorbitol acts as an osmotic driver, pulling extracellular fluid into the neuron and causing axonal and nerve trunk swelling (10–12). The swollen nerve in patients with diabetes had been confirmed with the use of diagnostic ultrasound in previous morphological researches (13, 14).

It is well-established that peripheral neuropathy in diabetes is heterogeneous, consisting of a diverse group of syndromes. Entrapment neuropathies are highly prevalent in the diabetic population; nearly, one of three patients has one. Since the treatment might be surgical, entrapment neuropathies should be actively sought in every patient with the presentation of neuropathy (15, 16). Nerve decompression has been advocated for the alleviation of pain, restoration of sensory, and prevention of ulceration in the previous reports (17–21). Furthermore, acute improvement in intraoperative electromyographic recordings following nerve decompression in patients with symptomatic diabetic sensorimotor peripheral neuropathy had also been reported (22, 23). Nevertheless, the role of decompressive surgery in the management of painful DPN remains controversial since the previous studies were mostly retrospective case series, and the level of evidence was deemed inadequate (24, 25). Therefore, a randomized controlled trial (RCT) with high-level evidence was strongly recommended to determine whether patients with painful DPN would benefit from this procedure (26).

According to the literature review regarding nerve decompression for painful DPN, only two RCTs were identified. In the first trial reported by Macare van Maurik et al. from the Netherlands, surgical decompression was performed in a randomly lower limb, and the contralateral one served as a control. Pain improvement in the operated leg was observed in 73.7% of 42 patients 1 year after surgery (27). Similar positive results were also demonstrated in another single-blinded, parallel-group RCT conducted by Best et al. from Canada, in which 22 patients with painful DPN were included and randomized to either surgery (*n* = 12) or observation (*n* = 10) (28). In their study, pain was the primary outcome assessed with two measures, McGill pain visual analog scores and Neuropathy-Specific Quality of Life Scale (NeuroQol) pain item. The former changed significantly over time within the groups, and the NeuroQol pain sensitivity analysis significantly changed from baseline to 12 months, comparing intervention (nerve decompression) to control. In these two RCTs, standard medication treatments including analgesics were allowed to use if needed; however, the medication treatments were not recorded and assessed. To address this limitation, the Quantitative Analgesic Questionnaire (QAQ) will be used in our present trial to quantify the analgesic medication regimen and thus to preclude the confounding effects of analgesics on evaluating the efficacy of nerve decompression for pain relief in DPN (29). Furthermore, the assessment of sensory profiles, psychological status, and quality of life will be conducted in this clinical trial to comprehensively investigate the effect of triple-nerve decompression in the treatment of the patient with painful DPN in the lower extremities. In this study, triple-nerve decompression will be compared with conventional medication for clinical effectiveness in the treatment of painful DPN. We believe that the completion of this clinical trial would add solid evidence to the literature.

## Methods

### Study design and setting

This trial was designed in accordance with the Standard Protocol Items: Recommendations for Interventional Trials (SPIRIT) (30). This study is a single-center RCT and will be conducted in Shanghai Ninth People's Hospital, Shanghai Jiao Tong University School of Medicine. Participants will be recruited from the Department of Neurosurgery. Before enrollment, a diagnosis of painful DPN will be made based on the results of medical history, physical examination, and electrophysiological examination of peripheral nerves. After signing an informed consent, subjects will undergo a complete evaluation, including medical history taking, physical examination, blood tests, and electrophysiological examination. Details of the inclusion and exclusion criteria were provided in Table 1. As illustrated in Figure 1, subjects meeting the inclusion and exclusion criteria will be randomly allocated at a 1:1 ratio into surgical and non-surgical groups. The assessments and follow-up plans, in this study, are summarized in Table 2. Previous medication treatment for neuropathy will be required to be stopped for at least 1 week before being formally enrolled in this trial.

**Table 1 T1:** The criteria for inclusion, exclusion, and discontinuation.

**Inclusion criteria**
1. Diagnoses
Diagnosed with confirmed diabetes according to the 1999 WHO diagnostic criteria for type 2 diabetes
2. Age
40–70 years old
3. Neuropathy
Michigan Neuropathy Screening Instrument (MNSI) clinical examination score > 2
4. Blood glucose control
Fasting blood glucose < 8 mmol/L and glycosylated hemoglobin (HbA1c) < 8%
5. Neuropathic pain
i. Neuropathic pain is distributed in the sensory areas innervated by the common peroneal nerve, posterior tibial nerve, and deep peroneal nerve
ii. Pain symptoms last for more than 6 months
iii. VAS of neuropathic pain is higher than 4
6. Nerve electrophysiology
Decreased nerve conduction velocity presented in more than one nerve (common peroneal nerve, posterior tibial nerve, and deep peroneal nerve) of the lower extremities (≥2 standard deviations)
**Exclusion criteria**
1. Existence of medical history that would cause neuropathy
i. Comorbidities such as pernicious anemia, hypothyroidism, vascular disease of the lower extremities (disappeared or weakened of the pulse of dorsalis pedis artery, varicose veins, etc.),
ii. Traumatic or surgical history of the lower extremities
iii. Medication history such as vincristine, phenytoin, etc.
iv. History of heavy metal poisoning, etc.
2. History of alcohol or drug addiction or abuse within 1 year at the time of enrollment
3. Lumbar spinal stenosis or active radiculopathy from lumbar disc herniation
4. Edema of lower extremities caused by various reasons
5. Existence of severe hemorrhagic diseases or bleeding tendency.
6. Intolerant to surgery or analgesics due to dysfunction of heart, lung, liver, kidney, and other vital organs
7. Patients with mental disorders and other factors that affect compliance
8. Rheumatism and rheumatoid diseases
9. Patients who are participating in other clinical trials
10. Previous foot ulceration or amputation
**Discontinuation criteria**
1. Occurrence of severe complications, side effects, comorbidities or other special physiological changes, such as pregnant, that prevent the subjects from continuing to participate
2. Lack of compliance to the protocol by the subjects that render the data collection unreliable
3. Loss to follow-up

**Figure 1 F1:**
[figure not shown]
A study flow diagram.

**Table 2 T2:** Study protocol timeline per subject.

**Timeline**	**Screen phase^†^**	**Baseline**	**Follow-up phase**			
**General characteristics**	**1st visit**	**2nd visit**	**3rd visit/W1**	**4th visit/M1** ^‡^	**5th visit/M3** ^‡^	**6th visit/M6** ^‡^
Informed consent	•					
Demographic data	•					
Clinical diagnoses	•					
Medical records	•					
Vital signs	•		•	•	•	•
Physical examination	•		•	•	•	•
**Laboratory tests**						
Fasting blood glucose	•			•	•	•
HbA1c	•			•	•	•
Routine blood test	•			•	•	•
Routine coagulation test	•			•	•	•
Blood tests for hepatic and renal function	•			•	•	•
**Criteria**						
Inclusion criteria	•					
exclusion criteria	•					
**Treatment**						
Surgery		•				
Medication		•				
Complication		•	•	•	•	•
**Outcomes**		•				
VAS	•	•	•	•	•	•
QAQ^§^		•	•	•	•	•
Two-point discrimination	•	•	•	•	•	•
TCSS		•	•	•	•	•
Electrophysiological test	•				•	•
HADS		•			•	•
SF-36		•			•	•
Adverse events		•	•	•	•	•

† Subjects will be enrolled within 2 weeks after the screening phase. The results of blood tests and examinations within 14 days before signing the informed consent are acceptable in the screening phase.

‡ Both groups will be followed up at the same frequency after treatment. The time horizon of the follow-up is 14 days, that is, the patients are followed up within 7 days before and after the follow-up time point.

§ QAQ will be used to quantify the analgesic medication regimen weekly.

### Study goals and objectives

The purpose of this study is to examine the role of decompressive surgery in selected patients with painful DPN suggestive of nerve entrapment. The primary objective of this clinical trial is to evaluate the efficacy of triple-nerve decompression for relieving neuropathic pain of DPN in the lower extremities. In addition, this research will investigate whether restoration of co-existed dysesthesia, improvement of nerve electrophysiology, psychological status, and quality of life could be better achieved by nerve decompression compared with conventional medication. The analgesic medication regimen will be quantified and analyzed with QAQ, the results of which will serve as an adjunctive evaluating indicator of the efficacy of nerve decompression (29).

#### Primary outcome

The primary outcome will be measured by 50% responder rates, which is defined as the proportion of subjects with at least a 50% reduction of the mean weekly visual analog score (VAS) of pain from baseline after 6 months of treatment in this trial. Mean weekly VAS will be calculated from the average VAS within the last 7 days. The subjects will be instructed to describe the intensity of their pain using an 11-point scale ranging from 0 to 10, with 0 as “no perceptible pain” and 10 as “unbearable pain.” When the pain is distributed in bilateral lower limbs, VASs of both lower limbs will be averaged together to generate a mean pain score. Mean weekly VAS will be, in addition, evaluated 1 week (W1), 1 month (M1), and 3 months (M3) after treatment to track changes in pain intensity.

#### Secondary outcomes

##### QAQ

The QAQ is an instrument designed for the comprehensive quantification of patient-reported chronic pain medication regimens, including the calculation of percent adherence and generation of quantitative scores to estimate and track changes in medication use over time (29). The application of QAQ will be helpful for point assessment of individual subjects and tracking pain levels throughout the trial period.

##### Two-point discrimination

The TPD test is a quantitative assessment of tactile acuity, discriminating between the sensation of two points touching the skin surface and that of only one point. It has been reported to be a simple and cost-effective clinical examination to evaluate the onset and progression of diabetic neuropathy (31). In this trial, the TPD test is performed in three locations, including the anterior dorsum of the foot and the medial and lateral anterior plantar area. These three areas are correspondingly located in the sensory territories of the superficial peroneal nerve, and medial and lateral plantar nerves (Figure 2). The TPD test is performed according to the method described by Moberg (32).

**Figure 2 F2:**
[figure not shown]
Sensory territories of peripheral nerves in the lower extremities. The two-point discrimination test is performed in the sensory territories of the superficial peroneal nerve, medial, and lateral plantar nerves, including the anterior dorsum of the foot, and medial and lateral anterior plantar area.

##### Toronto clinical scoring system

The TCSS was initially developed as a clinical stratification method in a study of simple screening tests for DPN (33). Later on, the TCSS was validated as an instrument to reflect the presence and severity of DPN (34). There are six symptom scores (the presence or absence of foot pain, numbness, tingling, weakness, imbalance, and similar upper-limb symptoms), eight scores of deep tendon reflexes (bilateral knee and ankle reflexes, each graded as absent, reduced, and normal), and five physical examination scores performed at the first toe (the presence or absence of pinprick, temperature, light touch, vibration, and position perception). Grading of TCSS is as follows:≤ 5 indicates no neuropathy, 6–8 indicates mild neuropathy, 9–11 indicates moderate neuropathy, and ≥12 indicates severe neuropathy.

##### Electrophysiological tests

As described in our previous study (17), the electrophysiological tests are conducted by two skilled technicians with the employment of a Denmark Medtronic electromyogram in an indoor environment with a room temperature of 25°C. In the supine position, the subjects are instructed to relax their lower limbs, and their skin temperature is kept higher than 32°C. Bilateral motor nerve conduction velocity (NCV) and amplitude of both posterior tibial nerve and common peroneal nerve are conducted. Bilateral sensory NCV and amplitude of superficial peroneal nerve are performed.

##### Hospital anxiety and depression scale

Subjects are instructed to complete a questionnaire on HADS, which is a self-reported questionnaire to assess the psychological status of both anxiety and depression. HADS is developed for the non-psychiatric clinical setting and includes 14 items: half items for anxiety (HADS-A) and half for depression (HADS-D). Ranging from 0 to 21, the total score indicates the degree of either anxiety or depression: 0–7 indicate asymptomatic cases, 8–10 indicate doubtful cases, and 11–21 indicate definite cases (35).

##### The medical outcome study short-form 36-item questionnaire

SF-36 is widely used to assess the quality of life across a wide spectrum of diseases, including painful DPN (36). It is a self-reported questionnaire that includes eight subscales: physical functioning (PF), role-physical (RP), bodily pain (BP), general health (GH), vitality (VT), social functioning (SF), role-emotional (RE), and mental health (MH). These eight subscales construct physical and mental health summary measures (37).

Along with the mean weekly VAS, TPD and TCSS will be conducted at W1, M1, M3, and M6 after treatment. Electrophysiological tests, HADS, and SF-36 will be performed at M3 and M6, and QAQ will be used to quantify the analgesic medication regimen weekly (Table 2).

### Interventional procedure

Subjects in the non-surgical group are treated with conventional medication for diabetes and pain symptoms. The analgesic medication will be prescribed according to the consensus from multiple guidelines and systematic reviews (38–40). First-line medications for diabetic neuropathic pain include calcium channel a2δ ligands (Pregabalin or Gabapentin), serotonin and noradrenaline reuptake inhibitions (SNRIs) (Duloxetine), and tricyclic antidepressants (TCAs) (amitriptyline). For individualized treatment, comorbidities, potential drug interactions, and severity or frequency of side effects will be taken into consideration when choosing the same class of analgesics (Figure 3) (11, 41). The common doses and side effects of each drug are listed in Table 3 (42). The analgesic medication regime in each subject will be assessed with the use of QAQ (29).

**Figure 3 F3:**
[figure not shown]
Treatment of painful diabetic peripheral neuropathy. First-line treatments for painful DPN include several drug classes, such as anticonvulsants (pregabalin or gabapentin), serotonin and noradrenaline reuptake inhibitors (SNRIs; duloxetine), and tricyclic antidepressants (amitriptyline).

**Table 3 T3:** Pharmacotherapies for painful DPN.

**Classes**	**Drugs**	**Dose ranges**	**Side effects**
Anticonvulsants	Pregabalin	Up to 100 mg TID, escalate to 100 mg TID within 1 week of initiation, escalate to 300 mg BID after 2–4 weeks when insufficient pain controlled	Somnolence, blurred vision, dry mouth, edema, weight gain
	Gabapentin	1,800–3,600 mg/day, starting from 300 mg QD, increase to 300 mg BID and TID, then escalate at TID	Dizziness, fall, somnolence, edema, gait disturbance
SNRIs	Duloxetine	60 mg QD	Nausea, somnolence, decreased appetite, fatigue, constipation
TCA	Amitriptyline	10–150 mg/day, increase by 10–25 mg/day every 3–7 days based on tolerability	Orthostatic hypertension, dry mouth, urinary retention, constipation

Subjects in the surgical group will undergo triple-nerve decompression procedure within 2 weeks after randomization. Throughout the study period after surgery, subjects are allowed to use analgesics if they still suffer from diabetic neuropathic pain, which will be carefully assessed and differentiated from postoperative short-term incision pain. As described in our previous study (17), Dellon's triple-nerve decompression of posterior tibial nerves and common and deep peroneal nerves in bilateral lower extremities will be performed under general anesthesia by the same senior surgeon ([name]) (43). The procedures are briefly described as follows.

A curved incision will be made along the medial malleolus, followed by opening the total length of the flexor retinaculum to expose the underlying tibial nerve and vessels. The tibial nerve will be followed distally to reach its division into lateral, medial, and calcaneal branches. With retraction of the abductor hallucis muscle, the deep fascia and the septum between medial and lateral plantar nerves are cut, and the underlying nerves are thus released. A second incision is made longitudinally over the dorsum of the foot. The tendon of the extensor hallucis brevis muscle is exposed and excised to decompress the underlying deep peroneal nerve. A third incision is made obliquely across the fibular neck and exposes the deep fascia, which is lifted to identify the common peroneal nerve. With the peroneus longus muscle retracted anteriorly, the common peroneal nerve is decompressed by dividing the deep fascia and releasing a frequent fascial band beneath the muscle. Postoperatively, patients are instructed to flex and extend the ankles and knees for 3 weeks. Unburdened mobilization will not be permitted until 3 days later, and the use of a walker aid is encouraged.

### Sample size

According to previous reports, the 50% responder rate of nerve decompression plus conventional analgesics medication is about 85% (20, 44), while conventional analgesics medication is about 50% (42). Given a type I error probability of 5% and a 10% loss to follow-up, a sample size of 37 in each group (ratio = 1:1) is estimated to provide 90% power to detect the statistical difference between surgical and non-surgical groups.

### Follow-up

Subjects in the surgical group will be discharged about 1 week after surgery, and the stitches will be removed about 2 weeks later. As demonstrated in Table 2, the follow-up evaluations will be conducted in the outpatient clinic at four time points: W1, M1, M3, and M6. Electrophysiological tests, questionnaire of HADS, and SF-36 will not be performed at W1 since the time interval is too short for these evaluations. QAQ will be assessed *via* telephone or internet weekly. The time horizon of each visit is set to be 14 days (within 7 days before and after the follow-up time point). Subjects are instructed to contact the investigators promptly in case any adverse events (AEs) occur between the visits.

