### Safety considerations

For each subject enrolled, all the AEs will be recorded in detail from the beginning to the last visit. According to our and others' prior reports, the main complication of nerve decompression is the issue of incision healing, which can be well-managed by active dressing change (17, 27, 28, 45). The common AEs of analgesics include dizziness, drowsiness, ataxia, and so forth. The symptoms would be effectively reversed by changing or withdrawing analgesic medication (42). The data associated with the clinical safety of the study will be monitored quarterly by the Data Safety Monitoring Board (DSMB). Unanticipated serious AEs will also be reviewed by the DSMB on an urgent basis if needed. DSMB members are independent of this trial, consisting of physicians from different institutes in China. The reports of AEs are regularly submitted to the Institutional Review Board, and the decision will be made on whether the trial can be continued.

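### Adverse events between visits rest on the subject calling in, although every subject is already contacted weekly for the analgesic questionnaire and no adverse-event question is stated for that contact

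*Protocol article*

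**What the plan says.** The Follow-up section sets the clinic schedule: "the follow-up evaluations will be conducted in the outpatient clinic at four time points: W1, M1, M3, and M6". The AE row of Table 2 is marked at baseline and at those four visits, and a footnote says that both arms are followed equally often. Between visits the stated route is subject-initiated: "Subjects are instructed to contact the investigators promptly in case any adverse events (AEs) occur between the visits".

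The same section adds a weekly remote contact: "QAQ will be assessed *via* telephone or internet weekly". The Table 2 footnote gives its content: "QAQ will be used to quantify the analgesic medication regimen weekly". No question on AEs is attached to it.

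The surgical arm has two further contacts: "Subjects in the surgical group will be discharged about 1 week after surgery, and the stitches will be removed about 2 weeks later". No corresponding contact is stated for the non-surgical arm.

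Safety considerations commits to complete recording: "all the AEs will be recorded in detail from the beginning to the last visit". It names dizziness, drowsiness and ataxia as common drug AEs and says of them: "The symptoms would be effectively reversed by changing or withdrawing analgesic medication".

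**The concern.** The commitment is to record every AE, but for most of the six months the stated method is passive. The drug AEs that the protocol expects are ones it describes as reversible when the drug is changed or withdrawn. Such an event can begin and end inside one interval and be forgotten, or thought not worth mentioning, at the next visit. The weekly QAQ would then show an analgesic stopped or changed without the reason.

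The Randomization section accepts that subjects cannot be blinded, so willingness to call in can differ between arms, in a direction nobody can predict. The surgical arm also has an inpatient week and a stitch-removal contact in the wound-healing period, when the main surgical complication named in Safety considerations would show. In the same early weeks, Table 3 has the non-surgical arm's drugs being stepped up (amitriptyline every 3–7 days, a pregabalin escalation after 2–4 weeks).

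At stake is the completeness and comparability of the harm data, which readers will set beside the pain results when weighing surgery against medication. The Introduction makes drug side effects part of the case for surgery, so their recording matters here.

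**Working it through.** The plan gives no figure on AE capture to reproduce. The check is of the schedule.

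**Inputs.** Visits at W1, M1, M3 and M6, each with a window of 7 days either side (Follow-up, Table 2). Weekly QAQ contact (Follow-up). 74 subjects (Abstract; 37 per arm in Sample size). Assumption: W1, M1, M3 and M6 are days 7, 30, 91 and 182.

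**Intervals without a scheduled AE enquiry.** Gap = later day − earlier day. The extremes are the gap minus and plus 14 days, with both windows used in opposite directions.

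| Interval | Gap (days) | Weeks | Range with windows (days) | Weekly QAQ contacts strictly inside |
|---|---|---|---|---|
| W1 to M1 | 30 − 7 = 23 | 3.3 | 9 to 37 | 3 (days 14, 21, 28) |
| M1 to M3 | 91 − 30 = 61 | 8.7 | 47 to 75 | 8 (days 35 to 84) |
| M3 to M6 | 182 − 91 = 91 | 13.0 | 77 to 105 | 12 (days 98 to 175) |

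**Existing contacts.** 182 / 7 = 26 per subject. Of these, 3 + 8 + 12 = 23 fall between visits; the other three coincide with W1, M3 and M6. Over the trial, 26 × 74 = 1,924 before any loss to follow-up. An AE question on the weekly contact would shorten the longest interval without an enquiry from about 91 days to 7.

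**Extra contacts by arm.** Surgical: about one inpatient week, ending around W1, and one stitch-removal contact. Whether its two weeks are counted from surgery (about day 14) or from discharge (about day 21), it falls between W1 and M1. Non-surgical: none stated in that interval.

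**Size of any loss.** It cannot be derived, because the article gives neither an AE rate nor a reporting probability. To show how far it depends on assumption, let p be the probability that a subject reports a transient AE unprompted, and r the probability that an unreported one is recalled at the next visit. Capture = 1 − (1 − p)(1 − r).

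| p | r | Capture |
|---|---|---|
| 0.3 | 0.2 | 1 − 0.7 × 0.8 = 44% |
| 0.5 | 0.3 | 1 − 0.5 × 0.7 = 65% |
| 0.7 | 0.5 | 1 − 0.3 × 0.5 = 85% |
| 0.9 | 0.8 | 1 − 0.1 × 0.2 = 98% |

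All p and r are assumed. The spread, from a serious loss to almost none, shows only that the documents do not settle the matter.

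**The case against.** The case for the plan as written has force. AEs are collected on the same schedule in both arms, self-report supplements it, and a visit question about the time since the last visit would nominally cover all 26 weeks. An AE that leads to a drug change will often reach the prescriber. This is a journal article, and the full protocol may hold a script for the weekly contact. QAQ may be done by internet, so the contact need not be a conversation. The article states no between-arm test of harms.

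Most of this limits the point without removing it. The article does not leave the between-visit route open: it states self-report. An event that passes without a drug change, or with one the subject makes alone, has no prescriber to surface it. An internet form can carry the same question as a call.

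Stronger readings are tempting, and the documents do not support them:

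- *Drug harms are under-counted and the harm comparison is biased.* Neither is shown; without reporting rates, this is a risk only.
- *Visits cover only a fixed share of follow-up.* One could get 4/26 = 15% with a one-week recall, or about (1 + 3.3 + 4 + 4)/26 = 47% with a four-week recall. Both recall lengths are invented, and both figures count self-report as nothing.
- *Surgical harms are watched and drug harms are not.* The inpatient week is about 1 of 26 weeks. Wound problems after discharge rely largely on the same visits and self-report. Interventional procedure also allows analgesics after surgery, so missed drug AEs are not confined to one arm. The asymmetry is modest.
- *Table 2 splits harms by arm*, because "Complication" sits under Treatment and adverse events under Outcomes. The two rows are marked at identical time points with no arm restriction, and Safety considerations discusses incision healing within its account of AEs.

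**Conclusion.** The point holds as a modest weakness in safety ascertainment. The stated method relies on self-report across intervals of about 3, 9 and 13 weeks, while some 23 between-visit contacts per subject already exist with no stated AE enquiry. Transient, reversible drug AEs may therefore be under-recorded, and possibly unequally between unblinded arms. Neither the amount nor the direction of any difference can be computed from the documents.

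The conclusion assumes the nominal visit days above, and that the weekly contact contains only what the article says it does. If the full protocol already puts an AE question there, the article needs only a clarifying sentence. The primary efficacy analysis and the sample size are not affected.

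**What to change.** In Follow-up and Table 2, extend the weekly QAQ contact in both arms, with identical wording by telephone and on the internet form, by:

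1. one open question on any new health problem since the last contact; and
2. the reason for any analgesic started, stopped or changed since then.

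State that positive answers go promptly to the investigator for assessment and AE recording. Mark AE enquiry as weekly in Table 2, for example by a footnote like the one for QAQ. Keep the scheduled visit enquiry and the instruction to self-report.

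The cost is a minor amendment and one or two questions on contacts that already take place. The downsides are more trivial AEs on file, someone to read the internet replies, and some follow-up of positive answers, spread over at most about 1,924 contacts. No treatment rule changes.
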